#### Home-based exercise programme (HBEP)

The second intervention block implements a home-based training programme (HBEP). The training with various balance, functional, and strength exercises aimed to prevent falls by furthering the training progress made in the first intervention block using the TSEP. All home exercises are based on the exercises in the TSEP but do not require any technological equipment. With functional exercises such as heel and toe walk, squats, knee raises, calf raises, tandem walk and lunges, aspects of gait and lower limb strength relevant to everyday life will be trained. The difficulty of the exercises is progressively increased over the course of the intervention period via the following parameters: number of repetitions and sets, inclusion of dual task exercises, and reduction of the base of support. All exercises and training details are summarised in a manual. The instructions of the exercises for the 24 training sessions are given, on the one hand, via this manual and, on the other hand, via provided videos. The videos are provided online through a website. Based on the participants’ preferences and technical prerequisites, they can use their preferred means of training. In addition, the first two training sessions of HBEP take place in the therapy centres with one-to-one supervision (= 26 supervised training sessions in the study centres).

Within the HBEP period for participants of the INT group and between T_2_ and T_3_ for participants of both groups (INT and CTR), phone calls are made regularly for motivation, potential questions, and feedback. For additional motivation to participate in the study until the last measurement (T3), participants in both groups will receive vouchers for ongoing study participation (20€ after T1 measurement, 30€ after T2 measurement, and 50€ after T3 measurement).

### Statistical analyses

#### A-priori estimation of sample size

Based on Sherrington and colleagues [10], it is assumed that the intervention will reduce the number of falls by 23% in comparison to the control group. Based on recommendations by Robertson [47], a binominal regression analysis was used to estimate the required sample size. Using G*Power [48, 49], a regression analysis with group (INT/CTR) as independent variable and number of falls as dependent variable, and -23% as the assumed reduction of falls, yielded a required total sample size of 181 persons. Assuming that the study will have an overall dropout rate of 30% [10], a total number of 235 participants to be included in the study is estimated.

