**Fig. 1 Fig1:**
[figure not shown]
SPIRIT-Figure: Schedule of enrolment, interventions, and assessments (CTR = control group; HBEP = home-based exercise programme; INT = intervention group; TSEP = technology-supported exercise programme; X = relevant for INT and CTR; +  = only relevant for INT)

For the intervention group, T_0_ is a baseline assessment; T_1_ an assessment after finishing the technology-supported part of the intervention; T_2_ an assessment after finishing the home-based exercise programme; and T_3_ a final follow-up assessment 12 months after T_2_. In total, the training period of the intervention group comprises 2*24 units (48 sessions in total) with a training frequency of two planned training sessions of 30 min each per week. The intervention period of the technology-supported exercise programme is individually dependent on the time progress of the completed 24 sessions. Given the defined training frequency of two training sessions per week, the technology-supported exercise programme has a minimum intervention period of 12 weeks. If individual training sessions are cancelled, the intervention period may be extended, however, it is limited to a maximum of 16 weeks. Identical to the intervention period of the technology-supported exercise programme, the period of the home-based programme is then determined individually for each participant. Participants in the control group receive all four measurements. Participants in the control group are not offered any actions; they are instructed to maintain their activities as usual. The time periods between the T_0_, T_1_ and T_2_ measurements are defined as 16 weeks for the control group. Both groups end at T_3_ with a final follow-up assessment 12 months after T_2_. Figure 2 shows the detailed timeline for study participants. Participants in the control group will have the opportunity to participate in an optimized training programme using the hunova robot after the end of the study.

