
### Randomisation procedures

An equal number of participants in the intervention and control group will be determined for each study centre. For this purpose, all eligible participants draw a lot with either INT or CTR after the baseline assessment. The number of lots for INT and CTR is equal and limited. Drawn lots are not returned to the lottery pot until all lots have been drawn. The examiners of the centres have no influence on the allocation to the groups, a change between groups is not possible.

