#### Planned statistical evaluation of outcomes

An analysis of primary outcomes (i.e., number of falls and number of persons who have fallen) will be based on binomial regression analyses with demographic variables, physical activity, and health parameters as covariates. Analyses of secondary outcomes (SI and TUG) will be based on 2 × 4 ANOVA / ANCOVA with groups (INT/CTR) and time of assessment (T_0_, T_1_, T_2_ and T_3_) as factors, and will consider demographic variables, physical activity, and health parameters as co-variates. Significant main or interaction effects will be investigated further using Bonferroni post-hoc-tests. The significance level is set to *p* < 0.05.

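### Enrolling 235 and losing 30% leaves about 164 participants, not the required 181; the dropout allowance matches 181 × 1.30 where 181 / 0.70 = 259 was needed

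*Protocol article*

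**What the plan says.** Under the heading on a-priori estimation of sample size, the protocol article sets the effect to be detected: "it is assumed that the intervention will reduce the number of falls by 23% in comparison to the control group". A regression calculation in G*Power on that basis "yielded a required total sample size of 181 persons". The next sentence allows for attrition by assuming an "overall dropout rate of 30% [10], a total number of 235 participants to be included in the study is estimated". No inflation formula is printed.

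Nothing elsewhere in the article changes these figures. There is no second dropout rate, no rule for replacing participants who leave, and no other enrolment target. Two further statements bear on the point. The section on randomisation procedures says "An equal number of participants in the intervention and control group will be determined for each study centre". The study design section sets the period over which dropout accrues: "Both groups end at T_3_ with a final follow-up assessment 12 months after T_2"_.

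**The concern.** A dropout rate is a share of the people enrolled. To finish with a given number, that number has to be divided by the share expected to stay. Multiplying the required number by one plus the dropout rate adds 30% of the smaller figure, although 30% of the larger figure will be lost. At low dropout the two routes nearly agree; at 30% they do not.

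A reader will take 235 as the enrolment that secures 181 under the plan's own attrition assumption. If it does not, the trial is short of its target even when everything goes as planned, and before any doubt is raised about the effect size or the fall rate. An inconclusive result for falls, one of the primary outcomes and the one for which 181 was derived, would then be judged against a size that the design was never set to reach.

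**Working it through.** **Inputs**, all from the sample size section of the protocol article: required total n = 181; dropout d = 0.30; stated enrolment N = 235.

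**1. Reproducing the stated figure.**
- n × (1 + d) = 181 × 1.30 = 235.3, which rounds to 235. This matches the article.
- n / (1 − d) = 181 / 0.70 = 258.57, so 259. This does not match; it exceeds 235 by 24, about 10% of 235.

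The multiplication is inferred, since no formula is shown. Using 23% by mistake would also give the figure, because 181 / 0.77 = 235.06, and 23% stands in the same paragraph as the assumed fall reduction. Under either explanation, 235 does not follow from a 30% dropout rate.

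**2. What 235 delivers at 30% dropout.**
- N × (1 − d) = 235 × 0.70 = 164.5 remaining.
- Shortfall: 181 − 164.5 = 16.5 persons; 16.5 / 181 = 9.1%.

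**3. The dropout rate at which 235 is enough.**
- 1 − 181 / 235 = 0.2298, so at most 23.0%.

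**4. Enrolment needed at other rates (181 / (1 − d)).**

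| Dropout | Enrolment needed |
|---|---|
| 20% | 226.3 |
| 23% | 235.1 |
| 25% | 241.3 |
| 30% | 258.6 |

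**5. Effect on power (illustration).** The article gives neither the power nor whether the test is one- or two-sided, so the starting power is an assumption here. With information proportional to the number of participants and a two-sided 5% test,

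power at 164.5 = Φ((1.96 + z) × √(164.5 / 181) − 1.96), where z is the normal quantile of the power at 181 and √(164.5 / 181) = 0.953.

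| Assumed power at 181 | z | Power at 164.5 |
|---|---|---|
| 80% | 0.842 | 76.1% |
| 90% | 1.282 | 87.1% |
| 95% | 1.645 | 93.0% |

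A one-sided 5% test gives nearly the same: 76.6%, 87.4% and 93.2%.

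The figure of 181 itself cannot be rebuilt from the article, because power, sidedness, baseline fall rate and dispersion are not given. Steps 1 to 4 do not need it to be rebuilt.

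**The case against.** The strongest reply is that a participant who drops out is not lost entirely. Falls are recorded daily in a diary, and completed sheets are collected at each assessment, so someone who leaves after T1 or T2 has already supplied months of primary outcome data. If dropout were spread evenly over follow-up and falls were analysed with a person-time offset, each dropout would contribute half a follow-up on average. The information would then be 235 × (0.70 + 0.30 × 0.5) = 235 × 0.85, or about 200 person-equivalents, which is more than 181.

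Part of this stands: 164 is best read as the expected number of completers, and the information actually lost on the falls outcome may be smaller than 30%. It does not rescue the sentence. The article offers no such reasoning, names no offset or partial-data rule, and adds its dropout allowance as though dropouts were lost. Because sheets are handed in at visits and T3 comes 12 months after T2, someone who leaves in that interval may return nothing for the longest part of follow-up. The benefit is also less clear for the number of fallers.

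Two smaller objections are fair. The power figures rest on an assumed starting power and are not the trial's own. The fact that 235 is odd, and so cannot split equally between arms within every centre, is a minor side point: 235 is a planning estimate, and an odd recruited total would only leave one pot of lots partly drawn.

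It can also be said that the slip biases neither the estimate nor the type I error. That is true, and it limits the damage to precision and power.

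**Conclusion.** The concern holds. The three printed figures (181 required, 30% dropout, 235 enrolled) contradict one another, and a fuller protocol or analysis plan could not make 235 × 0.70 equal 181. The stated enrolment falls 24 participants short of what the plan's own assumptions call for. At 30% dropout it yields about 164 completers, 9.1% below the requirement. This conclusion rests only on the article's own numbers.

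The consequence for power is modest, about 3 to 4 percentage points if 181 gave 80% or 90% power. It is conditional on that starting power and on dropouts contributing no data. The mechanism, multiplying by 1.30, is the likely explanation but is not needed for the conclusion. The error still calls for correction, because it lies in the headline enrolment figure and is certain on the article's own terms.

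**What to change.** Correct the sentence on dropout in the sample size section. Either of these makes it true without enrolling anyone further:

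- With 235 enrolled and 30% dropout, about 164 participants are expected to complete the study; give the power for that number, computed with the same G*Power inputs that produced 181.
- With 235 enrolled, the required 181 are retained provided dropout does not exceed 23%.

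If the investigators rely on partial follow-up from dropouts, the sentence should say so and state how much information each dropout is assumed to contribute.

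If both the 181 target and the 30% rate are to be kept, the enrolment figure is 259, or 260 for equal arms, with an even number in each centre. The Data Availability section says that recruitment was still under way at publication, so this was open at that time, but it is not needed to put the statement right.

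The restatement costs one sentence and a slightly less favourable stated power. It changes nothing in the design or the analysis.

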#### Planned statistical evaluation of outcomes

An analysis of primary outcomes (i.e., number of falls and number of persons who have fallen) will be based on binomial regression analyses with demographic variables, physical activity, and health parameters as covariates. Analyses of secondary outcomes (SI and TUG) will be based on 2 × 4 ANOVA / ANCOVA with groups (INT/CTR) and time of assessment (T_0_, T_1_, T_2_ and T_3_) as factors, and will consider demographic variables, physical activity, and health parameters as co-variates. Significant main or interaction effects will be investigated further using Bonferroni post-hoc-tests. The significance level is set to *p* < 0.05.

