#### Questionnaires

To evaluate aspects of the intervention, several questionnaires will be administered at T_1_ (after finalising the first part of the intervention) or T_2_ (after finalising the home-based programme), and an exercise diary will be kept:• The general feedback to the technology-supported exercise programme and the general feedback to the home-based exercise programme are assessed based on custom self-developed questionnaires that aim to assess feasibility;• The Usefulness, Satisfaction and Ease of Use (USE) questionnaire, a validated and reliable instrument [42], is used to assess user satisfaction with the technology-supported exercise programme and the home-based exercise programme;• The Task Load Index (TLX), a validated and reliable questionnaire [43], is used to assess subjective effort during the technology-supported exercise programme and the home-based exercise programme;• The User Experience Questionnaire (UEQ) [44] is used to evaluate both parts of the intervention;• Based on a customised questionnaire, overall feedback to the study will be collected to assess the subjective evaluation of participating in the study’s intervention.• An ‘Exercise diary’ is used to evaluate the home-based exercise programme and subjective effort.

Lastly, as additional background information, overall health status and physical activity will be monitored throughout the complete intervention (i.e., between T_0_ and T_3_). Each month, physical activity will be assessed based on the German PAQ-50 + [45], and to assess health status, the EQ-5D-5L [46] will be used at T_0_, T_1_, T_2_ and T_3_.

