### Potential limitations and risk for bias

The recruitment of potential participants will be via Generali Health Solutions (GHS), who will address insured older persons of “Generali Deutschland Krankenversicherung AG” (Generali Germany Health Insurance AG) and its subsidiary who live in the close area of the participating study centres. They receive detailed study information. The recruitment process could potentially lead to a selective recruitment of those older adults who are intrinsically motivated to exercise and who are already physically active. The fact that our study included older adults with a higher fall risk (according to the Silver Index, > 40%), while still being able to do 30 min of physical activity, could potentially bias our results. This aspect should be kept in mind while interpreting the results of the study. All interested persons had to state that they were willing to be randomised in one of the two groups to minimise dropouts, particularly in the control group. Within the randomisation procedure, a random allocation of all available places for the study is made by drawing lots. The examiners of the centres have no influence on the allocation to the groups, a change between groups is not possible and group preferences are strictly not allowed. Since the therapists do both measurements and the supervision of the training sessions, blinding of assessors is not possible which yields an acceptable risk for bias. The measurements at T_0_, T_1_, T_2_ and T_3_ are standardised and performed in the same room in each study centre by the same assessor. Measurements should be scheduled at the same day of the week and at the same time of the day for the four measurements if possible. The control group does not receive any training treatment, but they obtain the opportunity to use an optimised training programme after the study is finished (including 1-year follow-up). The participants in the control group are instructed to maintain their usual physical activity during the study. Due to the potential bias and influence of different levels of physical activity, the amount is documented through the German PAQ-50 + during the study duration for both groups. With having a multi-centre study, a bias of regional differences should be minimised. Furthermore, health status of older adults can change over the study duration and influence participation, drop-out rate and results of the study. To gain insights here, the EQ-5D-5L is implemented.

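### The primary and secondary models adjust for physical activity and health without limiting them to values taken before randomisation, and the stated rationale points to during-study values

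*Protocol article*

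**What the plan says.** In the protocol article, *Planned statistical evaluation of outcomes* states that the two primary outcomes, number of falls and number of fallers, "will be based on binomial regression analyses with demographic variables, physical activity, and health parameters as covariates". The secondary outcomes, SI and TUG, are analysed by a 2 × 4 ANOVA/ANCOVA with the same three groups of covariates. No measurement time is attached to any covariate.

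*Questionnaires* describes how the two non-demographic covariates are collected: "overall health status and physical activity will be monitored throughout the complete intervention", a period defined there as T0 to T3. For activity, "Each month, physical activity will be assessed based on the German PAQ-50"+. For health, "to assess health status, the EQ-5D-5L [46] will be used at" T0, T1, T2 and T3.

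*Potential limitations and risk for bias* gives the reasons. For activity: "Due to the potential bias and influence of different levels of physical activity, the amount is documented through the German PAQ-50 + during the study duration", in both groups. For EQ-5D-5L: "health status of older adults can change over the study duration and influence participation, drop-out rate and results of the study".

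*Randomisation procedures* places the drawing of lots after the baseline assessment. T0 measurements, and the health questionnaire and medication data listed in *Assessments* as part of eligibility screening, therefore precede allocation.

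**The concern.** Covariates measured before randomisation can be adjusted for safely. Covariates measured afterwards cannot, if the arm or the outcome can change them. Both conditions are plausible here:

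- **Activity.** The intervention is 48 exercise sessions, and controls are told to keep their usual activities. Activity reported during the study can therefore differ between arms because of the assignment itself.
- **Health.** Falls are counted from T0 to T3. EQ-5D-5L at T1, T2 or T3 can be lowered by a fall that is already part of the outcome.

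A group coefficient conditional on such values is not the effect of being assigned to the programme. The hypothesis at the end of the *Background* section, that the intervention reduces fall incidence, concerns that total effect. The comparison would also lose the protection that randomisation gives. Both primary outcomes and both secondary outcomes use this covariate set, so the choice bears on every main result.

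**Working it through.** **Step 1: which values does the text point to?**

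| Covariate | Clearly available before the lot is drawn | Collected afterwards | Stated reason for collecting it |
|---|---|---|---|
| Demographics | Yes (screening) | – | – |
| Health | Yes: T0 EQ-5D-5L, screening questionnaire, medications | EQ-5D-5L at T1, T2, T3 | Health may change over the study |
| Physical activity | Not confirmed in the text | Monthly PAQ-50+, T0 to T3 | Differing activity levels during the study |

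The screening list in *Assessments* contains no activity measure. T0 is named explicitly for EQ-5D-5L but not for PAQ-50+. Figure 1, the assessment schedule, is not reproduced in the text available and may show one. The text therefore leans towards during-study values, most clearly for activity, but does not state them.

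**Step 2: what would follow if later values were used?**

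The plan gives no figure for this point to reproduce. The one input taken from it is the assumed 23% reduction in falls, a rate ratio of 1 − 0.23 = 0.77. Everything else is an assumption:

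- falls follow a negative binomial distribution with dispersion 0.5 and a control mean of 0.6 × 1.6 = 0.96 falls per person;
- the post-randomisation covariate M has SD 1 within arm and is shifted by *a* SD in the intervention arm;
- the log rate of falls changes by *b* per SD of M, with the total rate ratio held at 0.77;
- a baseline variable has a correlation of 0.6 with M within arm and its own slope of 0.1 on the log rate;
- 400,000 simulated participants per scenario.

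Adjusting for M but not for the baseline variable, the expected group rate ratio is 0.77 × exp[−*a*(*b* + 0.6 × 0.1)] = 0.77 × exp[−*a*(*b* + 0.06)]. Worked extremes:

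- *a* = 0.5, *b* = −0.4: 0.77 × exp(0.17) = 0.913 (simulated 0.911)
- *a* = 0.5, *b* = +0.4: 0.77 × exp(−0.23) = 0.612 (simulated 0.614)

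Simulated rate ratios after adjustment for M:

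| Arm shift *a* (SD) | *b* = −0.4 | *b* = −0.2 | *b* = +0.2 | *b* = +0.4 |
|---|---|---|---|---|
| 0.2 | 0.823 | 0.788 | 0.733 | 0.704 |
| 0.3 | 0.858 | 0.802 | 0.714 | 0.672 |
| 0.5 | 0.911 | 0.825 | 0.677 | 0.614 |

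Negative *b* means that more activity or better health lowers falls, and the effect is attenuated (0.79 to 0.91). Positive *b* means that more activity adds exposure to falls, and the effect is exaggerated (0.61 to 0.73). In the same scenarios the unadjusted ratio was 0.767 to 0.774, and the ratio adjusted for the baseline variable was 0.767 to 0.775.

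**Step 3: health as a consequence of falling.**

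Here M drops by *h* SD per fall and has no effect on falls:

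| *h* (SD per fall) | Unadjusted | Adjusted for M |
|---|---|---|
| 0.1 | 0.777 | 0.779 |
| 0.2 | 0.767 | 0.778 |
| 0.3 | 0.770 | 0.795 |
| 0.5 | 0.772 | 0.830 |

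The shift is small for small *h* and always towards 1.

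**The case against.** The strongest reply is that the protocol never says post-randomisation values enter the model. The covariate list and the collection schedule stand in different sections, and the link between them is the reader's. Which visit supplies a covariate is a detail that a condensed article may leave to the full protocol or the analysis plan. Baseline health data exist, and the article does not define its health parameters as EQ-5D-5L. A conventional 2 × 4 ANCOVA takes one covariate value per person, which fits baseline use. The limitations section can also be read as monitoring whether controls keep to their usual activity, and *Questionnaires* presents both measures as background information.

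Most of this stands, and it is why the point is conditional. It does not remove the point. The article itself chose these covariates, describes activity only through monthly measurement, and explains that measurement by bias arising during the study. A reader who follows the text could build the wrong model without departing from it.

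Two stronger readings are tempting and are not supported:

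- **That the plan commits to post-randomisation adjustment.** No section says which values are used.
- **That adjustment necessarily removes part of the benefit.** The table shows that it can also inflate it. One could assume that a share *m* of the log effect runs through activity or health. That gives 0.77^(1−*m*) = 0.82, 0.88 and 0.94 for *m* = 25%, 50% and 75%, with sample-size multiples 1/(1−*m*)² of 1.8, 4 and 16. The arithmetic is right, but nothing in the documents supports any value of *m*. The mechanism the article stresses is muscle function, balance control and gait, none of which is a listed covariate.

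**Conclusion.** The point holds conditionally. The covariates in the primary and secondary models are not limited to pre-randomisation values, and the stated reasons for collecting activity and health data point to during-study values. If those are used, the group coefficient is not the effect of assignment.

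The size cannot be determined from the documents. The range of 0.61 to 0.91 around a true 0.77 rests wholly on assumed arm shifts of 0.2 to 0.5 SD and slopes of ±0.2 to ±0.4 per SD. It illustrates the count outcome only. It shows that the direction is open and that the distortion could matter in either direction; it is not an estimate of the bias in this trial.

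This should be fixed before analysis. Confidence is moderate, because an analysis plan that is not shown may already restrict the covariates to T0.

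**What to change.** In *Planned statistical evaluation of outcomes*, state that only values measured before the lot is drawn enter the primary and secondary models: demographics, T0 EQ-5D-5L or the screening health data (naming which), and PAQ-50+ only if it was completed at T0. If no pre-randomisation PAQ-50+ exists, leave activity out of these models. Reserve later PAQ-50+ and EQ-5D-5L values for description or for a labelled exploratory mediation analysis.

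The cost is about one sentence and no new data for health or demographics. The possible loss is activity as a covariate, if it was not measured at T0. The article reports that recruitment was still ongoing, so a T0 questionnaire could be added for participants not yet randomised, but this would not supply values for those already allocated.

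### Binomial regression is named for both primary outcomes, but it fits only the number of fallers and not the number of falls

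*Protocol article*

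**What the plan says.** Under Planned statistical evaluation of outcomes, the protocol article sets out "An analysis of primary outcomes (i.e., number of falls and number of persons who have fallen" and assigns one method to both: the analysis "will be based on binomial regression analyses with demographic variables, physical activity, and health parameters as covariates". No denominator, offset, dispersion term or robust variance is named there or elsewhere.

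Under A-priori estimation of sample size, "a binominal regression analysis was used to estimate the required sample size". The calculation is described as "a regression analysis with group (INT/CTR) as independent variable and number of falls as dependent variable". The effect is a relative reduction in falls: "it is assumed that the intervention will reduce the number of falls by 23% in comparison to the control group". The result is that it "yielded a required total sample size of 181 persons". Power, sidedness, control fall rate and dispersion are not given.

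The Fall diary section has participants record events daily from T0 to T3, so repeat falls are captured and no maximum per person applies. Under Study design, the intervention arm takes 24 to 32 weeks to reach T2 and the control arm is fixed at 32 weeks. Both arms then have a further 12 months to T3.

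**The concern.** Binomial regression models successes out of a known number of trials. Whether a participant fell at all is such an outcome. The number of falls is not, because a person may fall several times and no number of trials is defined. The fall count is one of the two primary outcomes and the quantity on which the 23% target is set.

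This is more than detail left to a later plan. The article positively names a model, names it twice, and the model does not match one of the two outcomes it is meant to serve. An analyst following the text would have to improvise, and the obvious ways of doing so have different consequences for the primary result.

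**Working it through.** **1. The plan's own figure.** Inputs from the article: rate ratio 0.77 (23% fewer falls), 1:1 allocation, significance level 0.05, total 181. Power, sidedness and control rate are missing, so 181 cannot be checked strictly. One can only ask which control mean μ0 would produce it. With a Poisson model, N = 2(zα + zβ)² (1/μ0 + 1/μ1) / (ln RR)², μ1 = 0.77 μ0 and (ln 0.77)² = 0.0683:

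- two-sided, 80% power: (1.960 + 0.842)² = 7.85, so N = 2 × 7.85 × 2.299 / (0.0683 μ0) ≈ 528/μ0, and N = 181 needs μ0 ≈ 2.9 falls per person;
- one-sided, 80% power: μ0 ≈ 2.3;
- two-sided, 90% power: μ0 ≈ 3.9.

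Read instead as a 23% relative cut in the proportion of fallers, about 75% control fallers gives 184 (one-sided, 80% power). Several unstated inputs land near 181, so the figure does not reveal which model was run.

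**2. Literal route A: any fall, yes/no.** This is the fallers outcome again. In a simulation (90 per arm, 590 diary days, gamma-Poisson falls, 1,000 trials per setting), type I error was 4.4 to 4.8%, so validity holds. The cost is information: at a true rate ratio of 0.77, power was 7 to 15%, against 16 to 28% for negative binomial regression on the same data.

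**3. Literal route B: falls out of diary days, plain binomial variance.** Falls are rare per day, so this is in effect Poisson. If the variance is μ + kμ², the standard error is too small by a factor √(1 + kμ), and the true two-sided error at a nominal 5% is 2[1 − Φ(1.96/√(1 + kμ))]:

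- μ = 0.6, k = 0.5: √1.3 = 1.140, giving 8.6%;
- μ = 1.0, k = 1: √2 = 1.414, giving 16.6%;
- μ = 1.5, k = 2: √4 = 2, giving 32.7%.

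A simulation of 20,000 null trials per setting, with 82 or 90 per arm (235 × 0.70 / 2 ≈ 82), gave 8.2 to 32.8% over the same range. The simulation of step 2, fitting the falls-per-day binomial model under no effect, gave:

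| Mean, k | Model SE | Empirical SE | Type I error |
|---|---|---|---|
| 0.85, 0.5 | 0.163 | 0.192 | 9.7% |
| 0.85, 1 | 0.163 | 0.231 | 16.6% |
| 1.6, 1 | 0.119 | 0.191 | 20.8% |
| 1.6, 2 | 0.120 | 0.237 | 33.2% |

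Negative binomial regression held 4.5 to 6.0% in the same settings. All means and k values are assumptions, and none of these models carried covariates.

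**4. Observation time.** The shortest intervention course is 24 + 52 = 76 weeks, and the control course is 32 + 52 = 84 weeks. With no effect at all, a raw count could be 1 − 76/84 = 9.5% lower in the intervention arm, so the count model needs a person-time offset.

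**5. What 181 gives under a negative binomial model.** N = 2(zα + zβ)² [1/μ0 + 1/μ1 + 2k] / (ln RR)². For μ0 = 0.8 and k = 1: 2 × 7.85 × (1.250 + 1.623 + 2) / 0.0683 ≈ 1,120 at 80% power, two-sided. For k = 0.5 to 2 the total is 891 to 1,580 at μ0 = 0.8, and 560 to 1,250 at μ0 = 1.6. With 181 analysed, power is 16 to 25% at μ0 = 0.85 and 19 to 36% at μ0 = 1.6.

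**The case against.** The best reply is that a word was dropped. The sample-size paragraph takes the number of falls as the dependent variable, uses a percentage reduction in falls as the effect and cites a recommendation for the method, all of which fits negative binomial regression. On that reading neither literal route is ever taken. This stands as a real possibility, but it does not rescue the text: the word is absent in both places, and a negative binomial model would be wrong for the yes/no fallers outcome that shares the sentence.

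A second reply is that neither literal route is written down. Falls and fallers are listed separately, so collapsing the count is not stated, and a binomial-family model can carry a dispersion term or robust standard errors that an analysis plan might specify. That also stands. The two routes are conditional readings, and only the second threatens the error rate.

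A third reply concerns size. The documents give no fall rate, variance or dispersion; the Background reports only the share of older people who fall. With k = 0 the Poisson-like standard error would be about right. The planned covariates could also absorb some between-person variation: at mean 1.0, type I error falls from about 17% at k = 1 to 11% at k = 0.5 and 8% at k = 0.25. In favour of some overdispersion, the Background describes risk from above 30% to beyond 50%, and the trial enrols anyone with a Silver Index above 40%, so participants will differ in risk. That makes it plausible without fixing its amount.

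**Conclusion.** The primary analysis is wrongly stated for the number of falls and must be corrected whichever explanation applies. That conclusion needs no assumption about fall rates.

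The consequences are conditional. If negative binomial was meant, the fault is one of wording, plus the need for a separate model for fallers. If the text is followed by coding any/none, type I error is sound but repeat falls are lost and the two primary outcomes become one analysis. If it is followed per diary day with plain binomial variance, type I error is about 8 to 33%, assuming a mean of 0.6 to 1.5 falls per person, k of 0.5 to 2 and no covariate adjustment; it is lower with smaller k or informative covariates.

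A reader might infer that the trial will report intervals that are too narrow, or that 181 has been shown to be wrong. The documents support neither. They state no variance estimator and no dispersion, and they omit the inputs needed to test 181.

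**What to change.** In Planned statistical evaluation of outcomes, replace the single model by two statements: *Number of falls: negative binomial regression, log link, log of observed diary time as offset, group effect as incidence rate ratio with 95% CI. Number of fallers: logistic or log-binomial regression.* The planned covariates can stay in both.

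In A-priori estimation of sample size, do not merely change the word, since that could misreport how 181 was obtained. State the model actually used and its power, sidedness, control fall rate and dispersion. If it was not a negative binomial calculation, give the power that 181 analysed participants provide under that model.

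No new data are needed, because the diary already supplies counts and observed time. The costs are somewhat wider intervals than under a plain binomial variance and, probably, a less favourable stated power.
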